All AIP subtypes respond dramatically to steroid treatment (up to 99% in the different cohorts) (11–14), but the optimal dose to induce remission remains controversial. Reported induction doses have ranges between 30 and 60 mg daily (11–14) Recently, other therapeutic options, that induce B-cell depletion, have also been employed in inducing AIP remission, with promising results (15, 16). In a cohort from France, the reported efficacy was 94% with two infusions given in most patients (17). However, in spite of the dramatic response to initial treatment, the risk of relapse within 1 year from disease remission ranges between 30 and 50% (12), being higher in type 1 than in type 2 AIP patients (12). Several risk factors for AIP relapse have been proposed, but have not been validated prospectively (11, 12, 18, 19). Due to the high frequency of relapse after induction, some authors recommend maintenance treatment with low-dose steroids or immunomodulators, but the patient group that would benefit from maintenance is currently unknown (20–26).

Thus far, data on the epidemiology and natural history of AIP are still scant due to its rarity and its relatively recent appraisal. Most of the data comes from Asian or North-American cohorts, while data on large European cohorts are lacking. As a consequence, treatment options applied in Europe are largely based on retrospective studies from Asian and North-American patients.

We established the PrescrAIP (A Pan-European Study on Current Treatment Regimens of Auto-immune Pancreatitis) study network to retrospectively describe the current status of AIP treatment in Europe on a large scale. In addition, our effort will create the opportunity for a subsequent international prospective registry that will be able to provide definite answers in the future. In particular, in this retrospective multicentre study, we aim to define and compare the AIP treatment regimens used throughout different European centers, highlighting their differential impact on disease remission and long-term outcomes. These results will foster our knowledge of this rare disease, yielding to better patient care.

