### Study Endpoints

Our primary endpoints consist of remission of disease (defined as the absence of clinical symptoms and the resolution of pancreatic abnormalities on imaging), relapse of disease, relapse rates compared between patients with a low or a high dose regimen, cumulative maintenance therapy dose and relapse-free survival time. Our secondary study endpoints are gold standard diagnostic tools of AIP compared to U-AIP, the prevalence of pancreatic exocrine insufficiency and the cumulative incidence of pancreatic ductal adenocarcinoma. The diagnosis of diabetes mellitus [as defined by the American Diabetes Association (27)] either before or after steroid treatment is our tertiary study endpoint.

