### Statistical Analysis

Continuous, non-normally distributed values will be presented as median and interquartile range (IQR), unless otherwise specified. Discrete variables will be presented as frequency (percentage). Normal distribution of continuous variables will be assessed with the Kolmogorov–Smirnov algorithm. Normally distributed variables among the different groups will be compared using the Student's *t*-test. Non-normally distributed variables will be compared using the Mann–Whitney *U*-test. Categorical variables will be analyzed by the Fisher's exact test or chi-square test.

To compare remission rates, relapse rates, relapse-free survival and long-term outcomes between participants, we will stratify participants according to the date of diagnosis, meeting the different diagnostic criteria, the type of treatment, the glucocorticoids starting dose, the cumulative dose, tapering speed, and treatment with maintenance treatment.

Moreover, to assess the impact of the treatment effect being part of the diagnostic criteria, we will perform sensitivity analyses comparing the study outcomes between those classified as AIP regardless of the steroid trial, and those in whom the diagnosis was dependent on the steroid trial. Sensitivity analyses will also be performed to compare the study outcomes including or excluding individuals that do not meet any available diagnostic criteria, and those classified as NOS-AIP.

Kaplan-Meier curves will be used to assess time-to-relapse. Time-to-relapse will be compared between subgroups using the log-rank test. Univariable and multivariable analyses with a backward selection procedure will be performed to identify possible predictors for relapse, based on a Cox-proportional hazards regression model. A significance threshold of *P* < 0.05 will be used.

Data from national pancreatic cancer registries will be used to determine age- and sex-specific incidence rates for pancreatic ductal adenocarcinoma. Standardized incidence ratios (SIRs) will be then calculated by obtaining the ratio of the observed to the expected number of cases, and 95% confidence intervals (95% CIs).

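### Relapse and relapse-free survival are separate primary endpoints, but only a Kaplan-Meier time-to-relapse analysis is named; with deaths censored it would overstate absolute relapse risk and would not give relapse-free survival

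*Protocol article*

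**What the plan says.** Study Endpoints lists five primary endpoints: remission, relapse of disease, relapse rates under low- and high-dose regimens, and finally "cumulative maintenance therapy dose and relapse-free survival time". Relapse and relapse-free survival are therefore separate items in the same list.

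Statistical Analysis keeps them apart at first: "To compare remission rates, relapse rates, relapse-free survival and long-term outcomes between participants, we will stratify participants". The time-to-event methods that follow all concern relapse alone. The estimator is given by "Kaplan-Meier curves will be used to assess time-to-relapse" and the test by "Time-to-relapse will be compared between subgroups using the log-rank test". Predictors of relapse are to be sought by a procedure "based on a Cox-proportional hazards regression model".

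The shown text does not define relapse-free survival, does not say whether death before relapse is an event or a censoring, and does not mention competing risks. Assessment Variables refers the reader to Appendix 1 for definitions.

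**The concern.** Relapse-free survival and time-to-relapse are different quantities unless nobody dies before relapsing. In common usage the first counts death as an event and the second does not. When death is censored, Kaplan-Meier treats a patient who has died as someone who could still relapse later. One minus the curve then estimates relapse in a hypothetical population without deaths, and it exceeds the proportion who actually relapse.

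Absolute risks matter here because the Discussion and its conclusion present the study as a description of the natural history of the disease. Diagnoses run from 2005 and the Discussion says that many patients have long follow-up, so deaths before relapse have time to accumulate. A reader of a published percentage would need to know whether deaths were in it.

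**Working it through.** The article states no event rate, sample size or mortality for its own cohort, so there is no planned figure to reproduce. The calculation is an illustration of size.

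**Inputs**
- Relapse in year 1: 30%. The Introduction says "the risk of relapse within 1 year from disease remission ranges between 30 and 50" per cent, and this is the lower end. The hazard is h1 = -ln(0.70) = 0.357.
- Relapse hazard after year 1: h2 = 0.06 per year (assumption).
- Death hazard: m = 0.03 per year, range 0.02 to 0.05 (assumption).

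**Formulas at T years**
- One minus Kaplan-Meier, deaths censored: 1 - exp(-[h1 + h2(T - 1)]).
- Cumulative incidence of relapse, death competing: h1/(h1 + m) × [1 - exp(-(h1 + m))] + exp(-(h1 + m)) × h2/(h2 + m) × [1 - exp(-(h2 + m)(T - 1))].
- Relapse or death: 1 - exp(-[h1 + h2(T - 1) + mT]).

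**Numbers put in, T = 10, m = 0.03**
- One minus Kaplan-Meier: 1 - exp(-0.897) = 59.2%.
- Cumulative incidence: year 1 gives 0.357/0.387 × (1 - 0.679) = 29.6%. Years 2 to 10 give 0.679 × 0.06/0.09 × (1 - exp(-0.81)) = 25.1%. The sum is 54.7%.
- Relapse or death: 1 - exp(-1.197) = 69.8%.

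**Results, m = 0.03, with the range for m = 0.02 to 0.05 in brackets** (differences taken before rounding)

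| Years | One minus Kaplan-Meier | Cumulative incidence | Overstatement, points | Relapse or death | Excess over one minus Kaplan-Meier, points |
|---|---|---|---|---|---|
| 5 | 44.9% | 43.3% | 1.7 (1.1-2.7) | 52.6% | 7.7 (5.2-12.2) |
| 10 | 59.2% | 54.7% | 4.5 (3.1-7.1) | 69.8% | 10.6 (7.4-16) |
| 15 | 69.8% | 62.0% | 7.8 (5.4-11.9) | 80.7% | 11.0 (7.8-15.9) |

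**Sensitivity to timing.** Suppose instead that all relapse falls in year 1, at 30% to 50%, with annual death risks of 1% to 5%. The overstatement is then only 0.1 to 1.1 points and does not grow with follow-up. The difference between the two endpoint labels does grow. With 30% relapse and 2% deaths per year, Kaplan-Meier relapse-free stays at 70.0%, while relapse-free survival counting death is 0.70 × 0.98^5 = 63.3% at 5 years and 0.70 × 0.98^10 = 57.2% at 10. Early relapse therefore reduces the first problem but not the second.

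**The case against.** Four objections deserve weight.

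- **Relapse is itself a primary endpoint.** A time-to-relapse analysis therefore serves a stated aim. This stands: it would be wrong to call relapse-free survival the primary endpoint and the Kaplan-Meier analysis a mismatch for that reason alone.
- **Censoring of deaths is nowhere stated.** The authors may use the two terms as synonyms, and Appendix 1 or an unseen analysis plan may define them. This stands in part. That one outcome will be reported with two values is something a reader might infer, but the article does not say it. A definition elsewhere could settle the labels, but it would not change the estimator printed here. If death is an event, the curve is not time-to-relapse; if death is censored, one minus the curve is not the probability of relapse.
- **The regimen comparisons survive.** With deaths censored, the log-rank test and Cox model compare the cause-specific relapse hazard, which is a defensible target for comparing effectiveness. This stands. Gray's test addresses a different hypothesis, and there is no need to require it.
- **The size depends on assumed rates.** It does. Only the year-1 relapse risk comes from the article, and 15 years of follow-up is open only to the earliest diagnoses.

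A reader might also infer that cancer risk will be overstated, because Study Endpoints names "the prevalence of pancreatic exocrine insufficiency and the cumulative incidence of pancreatic ductal adenocarcinoma" and Kaplan-Meier is the only time-to-event estimator mentioned. The text does not support this. The Kaplan-Meier sentence is confined to relapse, and the only cancer analysis described is a standardized incidence ratio of observed to expected cases. No Kaplan-Meier cancer estimate is planned in the shown text, so none can be said to be too high.

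**Conclusion.** The point holds in a limited form. The endpoint list separates relapse from relapse-free survival, the named estimator fits neither as an absolute quantity once deaths occur, and the treatment of death is left open. The bias concerns absolute relapse percentages, and its direction is certain if deaths are censored. In the central illustration it is modest at 5 years and material by 10 to 15; with early relapse only, it is about a point or less. The difference between the two endpoint labels is larger, about 8 to 11 points in the central case. All of these sizes rest on the assumed death rate, and the central figures also on the assumed later relapse rate. The point should be corrected before analysis, but it does not undermine the comparison of regimens.

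**What to change.** In Study Endpoints and Statistical Analysis:

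1. State how a death before relapse is counted.
2. Report absolute relapse risk as cumulative incidence (Aalen-Johansen estimator) with death as a competing event.
3. Keep the log-rank test and the Cox model, described as cause-specific comparisons in which deaths are censored.
4. If relapse-free survival is kept, define it as time to relapse or death, whichever comes first, and estimate it by Kaplan-Meier.

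The cost is small. Dates of death or last contact are already needed for the person-years behind the standardized incidence ratios, so no new variable should be required. A little more analysis is needed, and the reported relapse percentages will be slightly lower, which should be explained when they are set beside published series that used one minus Kaplan-Meier.

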## Abstract

**Introduction:** Treatment of autoimmune pancreatitis (AIP) is based solely on consensus and has yet to become standardized. Consequently, therapeutic regimens vary greatly between countries and centers, and largely depend on the experience of the physician. At this moment, the optimal regimen for inducing disease remission and preventing relapse is unknown.

**Objectives:** The primary objective of this study is to describe current treatment regimens used in Europe, and to compare their effectiveness in inducing remission and preventing and treating relapse. The secondary objectives are: to identify risk factors for relapse; to assess the diagnostic accuracy of the Unified-AIP criteria; to assess the performance of the M-ANNHEIM score for predicting relapse; and to assess long-term outcomes including pancreatic exocrine insufficiency and pancreatic cancer.

**Methods:** This is an international, retrospective, observational cohort study, performed in over 40 centers from 16 European countries. Eligible are all patients diagnosed with AIP from 2005 onwards, regardless of the used diagnostic criteria. Data on study subjects will be retrieved from the hospital's electronic medical records and registered with a standardized, web-based, electronic case report form (eCRF). To compare the effectiveness of treatment regimens in inducing remission, preventing relapse, and treating relapse, subjects will be stratified in groups based on: type of therapy; initial therapy dose; cumulative therapy dose; therapy tapering speed and duration; and having received maintenance therapy or not.

**Ethics and Dissemination:** Ethical and/or institutional review board approvals are obtained by all participating centers according to local regulations. The study complies with the General Data Protection Regulation (GDPR). All manuscripts resulting from the study will be submitted to peer-reviewed journals.

**Conclusion:** This is the first pan-European retrospective registry for AIP. It will produce the first large-scale data on treatment of European patients with AIP, providing answers on the use and effectiveness of treatment regimens. In the future, this collaboration may provide a network for continuation into a prospective European registry.

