## Methods

### Study Design

This is an international, retrospective, observational cohort study including all AIP patients. We used the Pancreas2000 framework (www.pancreas2000.org) to create a study network starting with the six centers in the PrescrAIP core group. Additional European centers with expertise in the treatment of AIP patients have been recruited, accumulating to a total of 44 collaborating centers.

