### Data Collection

Patient data will be collected from the hospitals' medical records. Variables were selected to answer the research questions and meet the objectives of the study. Variables will be recorded in a REDCap-based (https://www.project-redcap.org) electronic datasheet (electronic case record form, eCRF), hosted by The North Denmark Region. The principal investigator of each site will ensure that the data in the eCRF are accurate, complete and legible. REDCap is a secure, online application designed to support data acquisition and storage by providing a shapeable interface for validated data entry.

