### Assessment Variables

At the time of inclusion, all relevant variables will be recorded in the eCRF. These will include variables on demography and epidemiology, disease characteristics (radiological, laboratory and clinical), the set of diagnostic criteria employed, treatment (type, dose, duration), and short and long-term clinical outcomes. The complete variable list and definitions are reported in Appendix 1. AIP subtypes will be defined following the analysis of the above-mentioned variables. Given that patients with elevated serum IgG4 but without other organ involvement or biopsy sample can potentially be misdiagnosed, a subgroup with these characteristics will be created. Then a sensitivity analysis with and without excluding this subgroup will be performed to evaluate potential differences in the outcomes.

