## Ethics and Disseminations

This study was reviewed and approved by the ethics committees of the centers in the PrescrAIP core group, namely those at the San Raffaele Scientific Institute (Milan, Italy), the South East Regional Committee for Medical and Health Research Ethics (Oslo, Norway), the Erasmus University Medical Center (Rotterdam, The Netherlands), the Aalborg University Hospital (Aalborg, Denmark), the Marmara University School of Medicine (Istanbul, Turkey), the Institute for Clinical and Experimental Medicine (Prague, Czech Republic), the Karolinska University Hospital (Stockholm, Sweden), and the Martin Luther University Halle-Wittenberg (Halle, Germany). In addition, participating centers had the protocol reviewed and approved wherever required by local regulations.

Patients' data will be collected retrospectively from pre-existing electronic patient records. Study data will then be collected and managed using a REDCap database hosted at Aalborg University Hospital, North Denmark Region, Denmark. All data will be coded (pseudonymized). The key to the coded data will be stored locally in the participating site, in a password-protected file controlled by the Principal Investigator, and separately from any research data. For the German centers data will be anonymized immediately. When data is exported from the REDCap system for analysis, the data will be made completely unidentifiable and potential identifier variables will be removed. Additional processing of already collected data for the purpose of scientific research is exempt from specific consent according to Articles 5(1)(b) and 89(1) of the General Data Protection Regulation (GDPR). The study adheres to the Declaration of Helsinki. No patient will be exposed to any inconvenience in relation to the present study because all data are obtained retrospectively. The findings of the study will be published in a peer-reviewed journal and disseminated at national and international conferences.

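### Relapse is dated from routine-care records with no common assessment schedule, so if surveillance differs between regimen groups and some relapses are silent, the planned time-to-relapse comparisons partly measure detection, and no stated sensitivity analysis would show it

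*Protocol article*

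**What the plan says.** The Study Design section states: "This is an international, retrospective, observational cohort study including all AIP patients". Under Data Collection, "Patient data will be collected from the hospitals' medical records", and the ethics section repeats that "Patients' data will be collected retrospectively from pre-existing electronic patient records". No visit or scan is set by the study.

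The primary endpoints under Study Endpoints include "remission of disease (defined as the absence of clinical symptoms and the resolution of pancreatic abnormalities on imaging), relapse of disease", together with relapse-free survival time. Remission therefore needs imaging as well as absence of symptoms. Relapse is named but not defined in the article. Assessment Variables says that "The complete variable list and definitions are reported in Appendix 1", and that appendix is not among the documents at hand.

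Statistical Analysis plans Kaplan-Meier curves, and "Time-to-relapse will be compared between subgroups using the log-rank test". A Cox model with backward selection is planned for predictors of relapse. Participants are to be stratified by, among other factors, "the type of treatment, the glucocorticoids starting dose, the cumulative dose, tapering speed, and treatment with maintenance treatment".

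The Abstract says that "therapeutic regimens vary greatly between countries and centers, and largely depend on the experience of the physician", and the Discussion describes countries and practices as very heterogeneous.

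**The concern.** In routine care a relapse enters the record when someone looks. A symptomatic relapse brings the patient in. A relapse visible only on imaging or in blood is recorded when a scan or test is done, and carries that date. As planned, Kaplan-Meier, log-rank and Cox analyses take the recorded date as the event time and count an unexamined patient as relapse-free.

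This does no harm to a comparison if all groups are examined equally often. If they are not, the comparison of regimens is also a comparison of surveillance. The article ties regimen to country and centre and says that practice differs widely, so equal surveillance cannot be assumed. At stake is the primary objective of comparing how well regimens prevent relapse. The more closely watched regimen would look worse than it is, and a real benefit of that regimen could be hidden.

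**Working it through.** The article gives no event count, group size or assessment interval, so there is no figure to reproduce. The check asks what the planned analysis shows when true relapse is identical in both groups.

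**From the article (Introduction):** relapse within 1 year of 30% to 50%. At the midpoint of 40% with exponential onset, h = −ln(1 − 0.40) = 0.511 per year.

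**Assumed, not in the article:** scans every 3 months in one group and every 12 in the other, with random phase; 20% or 40% of relapses silent; symptomatic relapse recorded 1 month after onset; none or half of the silent relapses in the less-watched group never found; censoring at 2 years.

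**Step 1, symptomatic relapse recorded by 1 year, both groups:** 1 − exp(−0.511 × 11/12) = 0.374.

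**Step 2, silent relapse recorded by 1 year with scan interval d:** F(d) = 1 − [exp(−h(1 − d)) − exp(−h)] / (h·d).
- d = 0.25: 1 − (0.6817 − 0.6000)/0.1277 = 0.360
- d = 1: 1 − (1 − 0.600)/0.511 = 0.217

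**Step 3, mixing with 40% silent:**
- closely watched: 0.6 × 0.374 + 0.4 × 0.360 = 0.368
- less watched, none missed: 0.6 × 0.374 + 0.4 × 0.217 = 0.311
- less watched, half of silent missed: 0.6 × 0.374 + 0.2 × 0.217 = 0.268

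With 20% silent, the same sums give 0.371, 0.343 and 0.321.

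**Step 4, apparent hazard ratio by simulation (less watched versus closely watched, true value 1):**

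| Silent share | Silent relapses missed in less-watched group | Detected at 1 year, close v less | Apparent HR |
|---|---|---|---|
| 20% | none | 37% v 34% | about 0.95 |
| 20% | half | 37% v 32% | about 0.83 |
| 40% | none | 37% v 31% | about 0.89 |
| 40% | half | 37% v 27% | about 0.68 |

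**Step 5, how far this depends on the assumptions:**
- Varying 1-year relapse over 30% to 50% takes the lowest value to 0.65.
- If silent relapses become symptomatic after a mean of 6 months, the values at 40% relapse shrink to about 0.91 to 0.97.
- If the less-watched group is scanned every 6 months, with 40% silent and none missed, the value is about 0.95.

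**Step 6, effect on the log-rank test.** A second simulation used 100 or 200 patients per group, follow-up uniform over 1 to 5 years, 1-year relapse of 30% to 50%, and a two-sided 0.05 level (sidedness assumed). Symptomatic relapse was dated at onset.
- All relapses symptomatic: false-positive rate 0.043 to 0.058, so no bias at any interval.
- Equal 3-month intervals: 0.040 to 0.061.
- Half silent and persistent, 3 v 6 months: 0.050 to 0.087. The HR is 1/1.06 to 1/1.04, or 0.94 to 0.96.
- Half silent and persistent, 3 v 12 months: 0.095 to 0.291. The HR is 1/1.17 to 1/1.11, or 0.85 to 0.90.

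**Step 7, would the stated sensitivity analyses show it?** They cover patients with raised IgG4 but no other organ involvement or biopsy, diagnoses that depended on the steroid trial, patients meeting no diagnostic criteria, and NOS-AIP. The mitigation described in the Discussion for uneven use of guidelines also concerns diagnosis and subtype. None separates relapses by how they were found.

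**The case against.** Four objections carry weight.

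1. **No stated link between surveillance and regimen.** A reader might infer that visit and scan frequency in fact depends on regimen and on time off drug, so that long tapers or maintenance are bound to look worse. The article does not say this. It says that regimens vary by centre and that practices are heterogeneous, and does not mention surveillance. Closer follow-up after stopping a drug is equally possible, so the direction for any given regimen is unknown. This stands, and the point is worded conditionally.

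2. **The definition of relapse is in an appendix not shown.** If it requires symptoms, the problem largely disappears (Step 6, first line). This also stands. But a definition fixes only what counts as relapse. Unless it requires symptoms, it does not equalise how often patients were examined.

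3. **The methods are standard.** Kaplan-Meier, log-rank and Cox are usual for a chart-review cohort, and the article calls itself descriptive and leaves definite answers to prospective work. That lowers expectations but does not remove the point, because comparing regimens is part of the primary objective and the article does list its sensitivity analyses.

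4. **The largest figure is one-sided.** The HR of 0.68 needs half of silent relapses to go unfound in one group only and never to cause symptoms. This stands: 0.68 is the edge of a range and not an estimate.

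**Conclusion.** The point holds in conditional form. Relapse is dated from routine records without a common schedule, in centres that differ in regimen and practice. The planned comparisons contain nothing that separates relapse from its detection.

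Bias requires two things that the article neither states nor excludes: surveillance that differs between the compared groups, and some silent relapses counted as events. Given both, with 40% relapse at 1 year, scans every 3 versus 12 months and 20% to 40% silent relapse, the apparent HR runs from about 0.68 to 0.97 when the truth is 1. Without silent relapse it is 1. The silent share, scan intervals and missed fraction are all assumptions.

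The documents do not support the stronger statements that surveillance does differ by regimen, that a particular regimen is disadvantaged, or that the bias is large. They do support a modest, inexpensive addition to the analysis.

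**What to change.** - **Classify each relapse** as symptomatic, or as found by imaging or serology in a patient without symptoms. Use the clinical, laboratory and radiological data abstracted, where these allow it.
- **Report visits and scans per patient-year** by regimen group. If these are similar, the concern largely falls away.
- **Repeat every regimen comparison of time-to-relapse** with symptomatic relapse only as the event. Do not use treated relapse as the event, since a scan-detected relapse that is then treated would stay in.
- **Keep this as a sensitivity analysis.** Early treatment of a scan-detected relapse can prevent symptoms in the closely watched group and bias the result the opposite way. Call a regimen difference robust only if both analyses agree.
- **Use censoring at the last informative assessment only as an additional sensitivity analysis.** If patients in one group return mainly when unwell, those who stay well are censored early, and relapse in that group is inflated.

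The cost is a mode-of-detection classification, assessment counts from records already being abstracted, and a repeat of planned analyses. The symptomatic-only analysis has fewer events and so less precision. Mode of detection may be unrecoverable where data are already anonymized. The ethics section says this is done immediately for the German centres, which are 12 of the 44 listed under Setting. The number of unclassified relapses should be reported by regimen group.
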